## Abstract

**Background:**

Coronavirus disease (COVID-19) has spread globally with far-reaching, significant, and unprecedented impacts on health and everyday life. Threats to mental health, psychological safety, and well-being are now emerging, increasing the impact of this virus on world health. Providing support for these challenges is difficult because of the high number of people requiring support in the context of a need to maintain physical distancing. This protocol describes the use of SMS text messaging (Text4Hope) as a convenient, cost-effective, and accessible population-level mental health intervention. This program is evidence-based, with prior research supporting good outcomes and high user satisfaction.

**Objective:**

The project goal is to implement a program of daily supportive SMS text messaging (Text4Hope) to reduce distress related to the COVID-19 crisis, initially among Canadians. The prevalence of stress, anxiety, and depressive symptoms; the demographic correlates of the same; and the outcomes of the Text4Hope intervention in mitigating distress will be evaluated.

**Methods:**

Self-administered anonymous online questionnaires will be used to assess stress (Perceived Stress Scale), anxiety (Generalized Anxiety Disorder-7 scale [GAD-7]), and depressive symptoms (Patient Health Questionnaire-9 [PHQ-9]). Data will be collected at baseline (onset of SMS text messaging), the program midpoint (6 weeks), and the program endpoint (12 weeks).

**Results:**

Data analysis will include parametric and nonparametric techniques, focusing on primary outcomes (ie, stress, anxiety, and depressive symptoms) and metrics of use, including the number of subscribers and user satisfaction. Given the large size of the data set, machine learning and data mining methods will also be used.

**Conclusions:**

This COVID-19 project will provide key information regarding prevalence rates of stress, anxiety, and depressive symptoms during the pandemic; demographic correlates of distress; and outcome data related to this scalable population-level intervention. Information from this study will be valuable for practitioners and useful for informing policy and decision making regarding psychological interventions during the pandemic.

**International Registered Report Identifier (IRRID):**

DERR1-10.2196/19292

## Introduction

### Background

Coronavirus disease (COVID-19), a severe acute respiratory syndrome caused by the SARS-CoV-2 virus (severe acute respiratory syndrome coronavirus 2; officially identified in January 2020 in Wuhan, China), is now a global pandemic with far-reaching, significant, and unprecedented impacts on human health and everyday life. The World Health Organization declared the COVID-19 outbreak a Public Health Emergency of International Concern [1] on January 30, 2020, with many countries globally struggling to adapt to its impact. The closing of schools and small and large businesses, extremely high unemployment rates, and the effects of quarantine are further stressors facing the global population due to COVID-19 [2].

Threats to mental health, psychological safety, and well-being are now emerging, increasing the impact of this virus on world health [3,4]. Over half of survey respondents in China rated the psychological impact of COVID-19 as moderate or severe, with 29% reporting significant anxiety symptoms and 17% reporting significant depressive symptoms [5]; these symptoms persisted after 4 weeks of the COVID-19 epidemic [6]. A number of factors may correlate with psychological impact, including female gender, student status, specific physical symptoms (eg, myalgia, dizziness, and coryza), and poor self-rated health status. A recent rapid review of 24 published studies on pandemics reported negative psychological effects, including posttraumatic stress symptoms, confusion, and anger [7]. Stressors included longer quarantine duration, infection fears, frustration, boredom, inadequate supplies, inadequate information, financial loss, and stigma.

In a study focused on health care workers (HCWs), over half had significant symptoms of depression, approximately 45% showed significant anxiety symptoms, and one-third experienced sleep disturbance and insomnia [8]. Correlates of symptomatology were related to exposure (eg, working in Wuhan, working on the front line) and demographic factors, including gender and occupation (eg, female, nurse). Although an important and inevitable public health measure during a highly infectious disease outbreak, quarantine is associated with a number of negative psychological and social effects (eg, posttraumatic stress, anger, fear, financial loss, and stigma) [7], and may serve as an additional risk factor. The literature describing the psychological impact of natural disasters suggests that a subset of people exposed to natural disasters struggle with clinically significant mental health conditions, including anxiety, depression, and substance use disorders [9-11]. Several risk factors were identified for the development of psychological conditions after disasters. In addition to the demographic factors described above, these include degree of exposure [12-16], gender [17-20], social stressors (eg, unemployment status [17] or low socioeconomic status [18]), as well as pre-existing mental health conditions [18,21,22].

Even at this early stage of the global pandemic, there is evidence of significant psychological effects among the general population, which may be more pronounced in certain groups (eg, female, socially stressed, frontline worker, pre-existing psychological disorder) [23,24]. Providing support for these challenges is difficult because of the high number of people requiring support in the context of a need to maintain physical distancing.

Mobile health technology offers a unique and innovative solution in this context. Specifically, this tool offers a convenient, cost-effective, and accessible means for implementing population-level interventions. Almost 90% of Canadians own a smartphone [25], and SMS text messaging is free to end users, does not require technical skill for use, and does not require expensive data plans. Text messages are also cost-effective to providers, costing cents per message to deliver.

Supportive text messages are associated with positive outcomes, including the reduction of depressive symptoms, increased abstinence duration in alcohol use disorder, and high user satisfaction, as reported in previous research. For example, in randomized controlled trials (RCT), patients with depression that received supportive text messages showed symptom reduction on a standardized self-report when compared to a similar patient group that did not receive text messages (with large effect sizes: Cohen *d*=0.85, Cohen *d*=0.67) [26,27]. In another RCT, to evaluate the effectiveness of an addiction-related supportive SMS text messaging mobile intervention in improving treatment outcomes for patients with alcohol use disorder, small to moderate effects were found for the cumulative abstinence duration. In addition, the intervention group's mean time to first day to drink was over twice the length of that of the control group (60 versus 26 days, respectively) [27]. In two user satisfaction surveys, over 80% of subscribers reported that a supportive SMS text messaging program improved their mental health [27,28]. Subscribers reported text messages made them feel more hopeful about managing issues (82%), in charge of managing depression and anxiety (77%,), and connected to a support system (75%); in addition, such messages improved their overall mental wellbeing (83%) [27].

### Objective

This protocol describes the implementation of the Text4Hope program (a low-cost, evidence-based, supportive SMS text messaging service) in Canada. The objective of the project is to implement a self-subscribing daily supportive text message program (Text4Hope) to close the psychological treatment gap and reduce anxiety and stress related to the COVID-19 crisis among Canadians. Our research questions include the following: (1) What are the prevalence rates of stress, anxiety, obsessive compulsive, and depressive symptoms in Canada related to the COVID-19 crisis? (2) What are the demographic correlates of stress, anxiety, obsessive compulsive, and depressive symptoms? (3) Will the Text4Hope program help reduce stress, anxiety, and depressive symptoms among Canadians experiencing psychological distress as a result of the COVID-19 crisis?

## Methods

### Evaluation Methodology and Measurement Plan

In the Text4Hope program, individuals self-subscribe to receive daily supportive text messages for 3 months by texting “COVID19HOPE” to [name]. The messages are aligned with a cognitive behavioral framework, with content written by mental health therapists as well as our research team members (authors MH and [name]). The following is an example of the messages sent: “When bad things happen that we can’t control, we often focus on the things we can’t change. Focus on what you can control; what you can do to help yourself (or someone else) today” [29]. The messages are preprogrammed into an online software that delivers messages at 9 AM each morning. At the onset of the first message, respondents are welcomed to the service and are invited to complete an online baseline survey capturing demographic information; COVID-19–related self-isolation/quarantine information; and responses on the Generalized Anxiety Disorder-7 (GAD-7) scale [30], Perceived Stress Scale [31], and the Patient Health Questionnaire-9 (PHQ-9) [32]. Survey questions were programmed into SelectSurvey.net, an online survey tool operated by the Alberta Health Services Evaluation Services Team. No incentives are offered to respondents. Participation in the program is entirely voluntary, and completion of the survey was not a prerequisite requirement to receive supportive text messages. Subscribers may opt out at any time by texting “STOP” to [name]. Survey responses will be stored within our regional health system (Alberta Health Services) Select Survey account, and data will be exported, stored, and maintained by the Research and Evaluation team within our health region. The supportive SMS text messaging project subscriber recruitment plan was based on the success of a Text4Mood program in Alberta that was launched in response to the Fort McMurray wildfire disaster in 2016. Text4Hope has been the subject of a wide-exposure communications campaign (TV, radio, internet, and print media), including the local provincial mental health foundation, the single provincial government health care provider Alberta Health Services (AHS). Additionally, Text4Hope was the subject of a specific COVID-19 mental health support media release by the Provincial Chief Medical Officer [33]. Ethics approval has been granted by the University of Alberta Health Research Ethics Board (Pro00086163).

### Sample Size Considerations

Based on previous experience using the technology, (ie, >10,000 recipients within 6 months), we expect about 300,000 Canadians to subscribe to the Text4Hope program over the next 6 months. Based on a response rate of 21.7% for our prior Text4Mood survey [27], we anticipate around 20,000 responses to the Text4Hope surveys per 100,000 subscribers.

### Outcome Measures

The primary outcome is changed scores at 6 and 12 weeks from baseline on the Perceived Stress, GAD-7, and PHQ-9 scales. The secondary outcomes are the following: (1) changes in prevalence rates for perceived stress, anxiety, and depression from the early phase of the COVID-19 pandemic to a later phase, as measured with the Perceived Stress, GAD-7, and PHQ-9 scales, respectively; (2) the interaction between primary outcomes and the demographic characteristics of subscribers as well as the date of subscription to Text4Hope relative to the phase of the pandemic in Alberta; and (3) subscriber satisfaction/experience.

### Proposed Timeline and Milestones

The first stage involved the creation and review of the supportive text messages (targeting stress and anxiety-related concerns to COVID-19), and the programming of the messages into the software. This stage was completed on March 20, 2020. The second stage involved the launch of the Text4Hope program, which occurred on March 23, 2020. The remainder of the project will be focused on data analysis and reporting.

### Hypotheses

Our hypotheses, based on previous research, are as follows: (1) High rates of stress, anxiety, and depression will be reported, affecting one-third to half of the general population; the 1-week prevalence rates for these disorders will increase as the pandemic continues, compared to rates in the early phase. (2) Specific risk factors will be found for the experience of distress during the pandemic, such as female gender, risk of exposure, and social determinants of health (eg, employment, housing). (3) The intervention will result in a 25% or greater reduction in perceived stress, anxiety, and depressive symptoms (as measured by the Perceived Stress, GAD-7, and PHQ-9 scales) at 6 and 12 weeks from baseline. (4) At least 80% of subscribers will express satisfaction with the Text4Hope program and perceive the daily supportive text messages as contributing to their overall mental well-being.

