## Discussion

The impact of the COVID-19 global pandemic on health, way of life, and psychological safety and wellbeing is difficult to overstate. The psychological impact on the general population, both during and after the crisis, requires the use of innovative techniques that can serve the high number of people requiring support, while respecting the need to maintain physical distancing.

The current protocol describes the use of mobile health technology as a convenient, cost-effective, and accessible means for implementing a population-level psychological intervention during the pandemic. This program is empirically supported by previous research results, showing good outcomes as well as high user satisfaction [26,27]. This project will evaluate outcomes with standardized, empirically validated questionnaires, and will also provide key information regarding prevalence rates of stress, anxiety, and depression in the Canadian population during the COVID-19 pandemic; demographic correlates of this distress; and outcome data related to a scalable population-level intervention. Information from this study will thus be critical for practitioners, as well as useful for informing policy and decision-making regarding psychological interventions during the COVID-19 pandemic. If Text4Hope is effective for the Canadian population, we will explore scale-up and national implementation, and will disseminate this program for adaptation for potential global use through the APEC Digital Hub for Mental Health [42].

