Limitations of this protocol include a lack of baseline data on stress, anxiety, and depression levels before self-isolation measures were implemented in Alberta; this was unavoidable as our study was initiated shortly after quarantine and self-isolation measures were introduced. Nonresponse bias may also affect the expected results, as program subscribers are a sample of the population, not the entire population of the province. Nonrespondents may differ in a systematic way compared to respondents. For example, they may differ in their baseline level of mental wellness, be more (or less) affected by the pandemic, or have limitations in literacy or English fluency. In view of the limitations noted above, any prevalence estimates must be interpreted with caution, and compared to the conventional baseline of subsequent conventional prevalence estimates. The authors also note that this protocol does not include a control group and this raises the question of specificity concerning hypothesis 3, which concerns reductions in perceived stress, anxiety, and depressive symptoms. Previous RCT work from this group has demonstrated the efficacy of supportive SMS text messaging in intervention groups, compared to control groups that did not receive supportive text messages; instead, the control group received the same survey requests as the intervention group in addition to a single text message every 2 weeks, thanking them for participating in the study [26,37]. Given the intention to provide support to the catchment population of this study and the prior evidence for efficacy, it would be unethical to include a control group in the current protocol. Nevertheless, prior studies did include subscriber satisfaction surveys, as does this protocol, and that measure will provide evidence for engagement of the subscribers with the program (simply put, if subscribers ignored the text messages, it is highly unlikely that there would be positive satisfaction survey results). In the current health implementation context of this protocol, the comparison of changes in outcome measures in relation to comparison with effect sizes from our prior work (together with an assessment of the degree of correspondence of subscriber satisfaction survey responses to changes in our outcome measures) will be a good indicator of subscriber engagement in the absence of a control condition. Despite these limitations and possible bias factors, our protocol will provide useful data about the mental health characteristics of individuals in the early stages of the COVID-19 pandemic. We expect that our results will represent an important initial source of information for government and health care planners in determining the nature and quality of services required to address mental health challenges arising during this pandemic, as well as future pandemics that employ self-isolation or quarantine measures. Specifically, planning for and implementing virtual care programs, including supportive SMS text messages, may be a fruitful approach to supporting isolated or quarantined individuals. In addition, we expect the supportive SMS text messaging intervention to have a positive effect on mental well-being and we will be able to measure this well within the expected sample size.

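### Prevalence is stated for Canada and the general population, and satisfaction for all subscribers, but the design observes only self-subscribed people who choose to answer an optional survey

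*Protocol article*

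**What the plan says.** Three places in the protocol article set the prevalence target.

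- Objective, research question 1: "What are the prevalence rates of stress, anxiety, obsessive compulsive, and depressive symptoms in Canada related to the COVID-19 crisis".
- Hypotheses, hypothesis 1: "High rates of stress, anxiety, and depression will be reported, affecting one-third to half of the general population".
- Discussion, which promises key information on "prevalence rates of stress, anxiety, and depression in the Canadian population during the COVID-19 pandemic".

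Evaluation Methodology and Measurement Plan describes the source of the data. There, "individuals self-subscribe to receive daily supportive text messages for 3 months", and "completion of the survey was not a prerequisite requirement to receive supportive text messages". The named promoters are the provincial mental health foundation, Alberta Health Services and the province's Chief Medical Officer, alongside TV, radio, internet and print. Sample Size Considerations takes a 21.7% response rate from an earlier survey and plans on roughly 20,000 responses per 100,000 subscribers. Results gives 60,000 completers out of 300,000.

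The limitations part of the Discussion says: "Nonresponse bias may also affect the expected results, as program subscribers are a sample of the population, not the entire population of the province". It adds that nonrespondents may differ systematically, including in mental wellness. It asks for care in reading prevalence estimates and for comparison with later conventional ones.

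On satisfaction, hypothesis 4 reads: "At least 80% of subscribers will express satisfaction with the Text4Hope program". The limitations then argue that favourable satisfaction results would be very unlikely if subscribers were ignoring the messages.

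**The concern.** The quantity named and the quantity observed differ by two selection steps: from the population to those who subscribe, and from subscribers to those who answer. Either step may depend on how distressed a person is. The service is offered to relieve distress, and research question 3 describes the people it hopes to help as Canadians in psychological distress because of the crisis. If distress raises the chance of entering and answering, the proportion scoring positive among respondents overstates the population rate, and more respondents will not correct that.

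What is at stake is how hypothesis 1 is read. A figure between one-third and half among respondents would appear to confirm a population rate, and the Discussion expects policy makers, government and health care planners to use the results.

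Hypothesis 4 has a similar gap. Its denominator is subscribers, but satisfaction is seen only in those who return a survey. The engagement argument in the limitations is weak for the same reason: subscribers who ignore the messages are unlikely to answer the survey, so they would mostly be absent from the satisfaction results.

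**Working it through.** **Inputs from the protocol article.** Expected subscribers 300,000 and completers 60,000 (Results); earlier response rate 21.7% and about 20,000 responses per 100,000 (Sample Size Considerations); hypothesised prevalence one-third to half and satisfaction 80% (Hypotheses).

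**1. The plan's own figure.** 60,000 / 300,000 = 20.0%, and 300,000 × 0.20 = 60,000, so the figures agree. The unrounded rate would give 300,000 × 0.217 = 65,100; the text rounds down to about 20%.

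**2. Sampling error.** The 95% half-width is 1.96 × √(p(1 − p)/n) with n = 60,000.
- p = 0.5: 1.96 × √(0.25/60,000) = 0.0040, or 0.40 points.
- p = 1/3: 1.96 × √(0.2222/60,000) = 0.0038, or 0.38 points.

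Random error is therefore negligible, and any material error will come from selection.

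**3. Self-selection.** Let o be the proportion positive among respondents. Let k be how many times as likely a distressed person is to subscribe and respond as a non-distressed person. Then

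true prevalence = o / (o + k(1 − o)).

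The article gives no value for k. The values below are assumptions, shown as a range.

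| k | observed 50% | observed 33.3% |
|---|---|---|
| 0.5 | 67% | 50% |
| 1 | 50% | 33% |
| 1.5 | 40% | 25% |
| 2 | 33% | 20% |
| 3 | 25% | 14% |

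Example: o = 0.5 and k = 2 give 0.5 / (0.5 + 2 × 0.5) = 0.33. At k = 2, a true 20% shows as 33% and a true 33% shows as 50%, so selection alone could place the result inside the hypothesised range. The row for k = 0.5 shows that the bias could also run the other way.

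**4. Hypothesis 4.** If 80% of respondents are satisfied and 20% of subscribers respond, satisfaction has been observed in 0.80 × 0.20 = 16% of all subscribers. For the other 80% of subscribers it is unknown.

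**The case against.** The strongest reply is that the article already says this. Its limitations paragraph gives as the reason for bias that subscribers are only part of the population, allows that nonrespondents may differ in mental wellness, advises caution, and calls for comparison with later conventional estimates. That is real disclosure, and it covers more than survey nonresponse. It does not, however, change research question 1, hypothesis 1 or the Discussion's promise. It also speaks of the province where the other passages speak of Canada. A caution about a target does not redefine the target.

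A second reply is that the consequence is limited. The primary outcome is within-person change at 6 and 12 weeks, and the prevalence outcome listed as secondary is a change between phases, not a level. This is correct, and it keeps the point away from the primary analysis. Research question 1 and hypothesis 1 still ask for a level.

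A third reply is that hypothesis 4 uses ordinary shorthand for survey results, and that the article also plans to relate satisfaction to outcome change. The shorthand is common, but both of those measures come from respondents only.

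Some stronger readings are tempting and are not supported:

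- *Subscribers are all help-seekers.* The article reports no motives and sets no symptom criterion, and the campaign was a mass one. Entry driven by distress is plausible but not established.
- *The study is confined to Alberta.* The named promoters are provincial and national rollout is described as a later step, but no passage restricts who may subscribe, and 300,000 Canadians are expected.
- *Worst-case nonresponse bounds give the size of the bias.* At 20% response, an observed 33% to 50% is compatible with anything from 7% to 90% among subscribers. Those bounds assume that all or none of the nonrespondents are positive. They address the second selection step only and are not evidence of actual bias.

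**Conclusion.** The point holds as a mismatch between the stated target and what the design can estimate. Prevalence among responding subscribers can be estimated very precisely. Prevalence in Canada or the general population cannot be estimated from the data described without bias of unknown size and, strictly, unknown direction. If distressed people are 1.5 to 3 times as likely to subscribe and respond, an observed 50% corresponds to a true 40% to 25%, and an observed 33% to 25% to 14%. That range rests wholly on the assumed ratio, which the article neither gives nor excludes. Hypothesis 4 has the same denominator problem, and the engagement argument offered in place of a control group gives little support. A reader might infer that the authors overlooked the issue or that the primary outcome is compromised by it. Neither follows: the limitations partly disclose it, and the primary outcome is change within persons.

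**What to change.** - Restate research question 1 and hypothesis 1 as the proportion screening positive among responding Text4Hope subscribers.
- Remove the general-population prevalence claim from hypothesis 1 and the Canadian-population claim from the Discussion, so that both agree with the caution already in the limitations.
- State hypothesis 4 for survey respondents, and report the response rate beside the result.
- Weaken the sentence that treats good satisfaction results as evidence that messages were not ignored.

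Optionally, add estimates raked to population margins as a sensitivity analysis, with a statement that this does not remove self-selection on distress. The number texting STOP can be reported over all subscribers as an opt-out count. It should not stand in for satisfaction or engagement, because people who passively ignore messages need never send it.

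The cost is rewording plus one count of subscribers and respondents. The downside is a narrower claim.

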We will evaluate the efficacy of Text4Hope with the reductions of perceived stress, anxiety, and depression at 6 weeks and 12 weeks. Data analysis will include the standard use of parametric and nonparametric techniques (eg, within-subject general linear models), including multiple comparison Type 1 error corrections. Power analysis with effect sizes based on [name] group research publications [26-28,36,37] indicates a sufficient effect size for the expected Text4Hope program subscriber sample size. As the sample size for the data set generated from this project will be large, in addition to the conventional statistics used in these projects, we plan to adopt a “big data” analysis approach to examine data-driven patterns. Using machine learning and data mining methods, we expect to capture the most powerful window on differences and high-order sets of potential interactions. With our program targeting 300,000 Canadians to self-subscribe, with an expected 60,000 completing the survey, we are confident that this project has adequate power for our basic cross-sectional approach. We will develop predictive models using baseline measurements (features) and machine learning algorithms (eg, the least absolute shrinkage and selection operator [LASSO], support vector regression [SVR], and random forest regression, etc [38-40]) to predict the efficacy of our intervention at 6 and 12 weeks, as measured by the change in assessment scores (eg, GAD-7, PHQ-9) compared to the baseline. We will perform a 10-fold cross-validation to evaluate the performance of the models. During cross-validation, the data will be randomly segmented into 10 folds, with each fold containing 10% of the data. For each iteration, 1 fold will be left out as the testing data and the remaining 9 will be the training data. Within each training session, another internal 10-fold cross-validation will be used to select the best features, algorithm, and corresponding hyperparameters as the model to be trained on this specific training session. The selected model in the training data will then be applied to the testing data. This procedure is crucial for predictive tools as the data being tested has never been seen in any way by the model. The performance of the models will be evaluated using the Pearson correlation between the predicted and actual reduction of the outcome measures.

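### Hypothesis 4 and the engagement argument speak of subscribers, but satisfaction is known only for the roughly 20% expected to answer a voluntary survey

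*Protocol article*

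**What the plan says.** **The claim.** Under Hypotheses, the fourth hypothesis is: "At least 80% of subscribers will express satisfaction with the Text4Hope program and perceive the daily supportive text messages as contributing" to their mental well-being. Outcome Measures lists satisfaction and experience of subscribers as the third secondary outcome. The Results section makes it the acceptability dimension of the evaluation, again for subscribers.

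**Who is measured.** Evaluation Methodology and Measurement Plan makes the survey voluntary, offers no incentive, and does not require it for receiving messages. Subscribers can leave at any time by text. Sample Size Considerations takes a 21.7% response from an earlier programme and concludes: "we anticipate around 20,000 responses to the Text4Hope surveys per 100,000 subscribers". The Results section repeats the rate in absolute numbers: "With our program targeting 300,000 Canadians to self-subscribe, with an expected 60,000 completing the survey".

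**The engagement argument.** The Discussion acknowledges that there is no control group and offers satisfaction as evidence of engagement, reasoning that "if subscribers ignored the text messages, it is highly unlikely that there would be positive satisfaction survey results". It adds two companion checks: comparison with effect sizes from earlier work, and agreement between satisfaction answers and change in the outcome scales.

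**The caveat.** The Discussion says that nonresponse may bias the results and that people who do not answer may differ systematically. The caution drawn from this names prevalence estimates. The later engagement argument carries no such caution.

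**The concern.** The hypothesis and the measurement have different denominators. A percentage of respondents is to be read against a threshold set for all subscribers, and four in five subscribers are expected to supply no answer. Whether someone answers a voluntary survey about a service plausibly depends on whether they used and liked it, so the missing answers cannot be presumed to resemble the observed ones.

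The engagement argument has the same weakness in a sharper form. It treats poor satisfaction results as the expected sign of ignored messages. Someone who ignores the messages is unlikely to fill in a voluntary survey from the same service. That person is missing from the satisfaction figure and does not pull it down.

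At stake are a secondary outcome, the acceptability result, and part of the support offered for reading symptom change (hypothesis 3) in a design without a control group. A report that over 80% of subscribers were satisfied could be published, and used for planning, while the experience of most subscribers was unknown.

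**Working it through.** **Inputs.** Subscribers 300,000 and completers 60,000 (Results section); 20,000 responses per 100,000 subscribers and an earlier response rate of 21.7% (Sample Size Considerations); threshold 80% (Hypotheses). The article gives no opt-out rate and no response rate specific to the satisfaction questions, so the 20% is carried over to them as an assumption and varied below.

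**Step 1. Reproduce the plan's figure.** 20,000 / 100,000 = 0.20, and 300,000 × 0.20 = 60,000, which matches. The unrounded 21.7% would give 300,000 × 0.217 = 65,100. The article's figure is an approximate one, so this is rounding down and not an error.

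**Step 2. Subscribers without a satisfaction answer.** 300,000 − 60,000 = 240,000, or 80%.

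**Step 3. Worst-case bounds for all subscribers.** Let r be the response rate and s the share satisfied among respondents. The lower bound counts every nonrespondent as not satisfied: r·s. The upper bound counts every nonrespondent as satisfied: r·s + (1 − r). At r = 0.20:

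| s among respondents | Lower bound | Upper bound | Share of nonrespondents who must be satisfied to reach 80%: (0.80 − r·s)/(1 − r) |
|---|---|---|---|
| 80% | 0.20 × 0.80 = 16% | 0.16 + 0.80 = 96% | 80% |
| 90% | 0.20 × 0.90 = 18% | 0.18 + 0.80 = 98% | 77.5% |
| 100% | 20% | 100% | 75% |

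**Step 4. Could any result settle the claim for subscribers?** To show it without assumptions, r·s must be at least 0.80, which is impossible unless r is at least 80%. To refute it, r·s + (1 − r) must fall below 0.80. At r = 0.20, even s = 0 leaves an upper bound of exactly 80%, so no result refutes it. At r = 0.217, s would have to be below (0.80 − 0.783)/0.217 = 7.8%.

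**Step 5. Other response rates, with s = 80%.** The 5% and 10% rows are assumed values, since follow-up response is not given.

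| r | Lower bound | Upper bound |
|---|---|---|
| 5% | 4% | 99% |
| 10% | 8% | 98% |
| 20% | 16% | 96% |
| 21.7% | 17.4% | 95.7% |

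**Step 6. Sampling error for comparison.** With 60,000 respondents and s = 80%, the 95% half-width is 1.96 × √(0.80 × 0.20 / 60,000) = 0.0032, about 0.3 percentage points. The interval from nonresponse is 80 points wide (96 − 16). Because that width is 1 − r, recruiting more subscribers at the same response rate does not narrow it.

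**Step 7. Illustration (assumed values).** Suppose 85% of respondents are satisfied and r = 0.20. If 80%, 70% or 50% of nonrespondents are satisfied, the all-subscriber figure is 0.17 + 0.80 × 0.80 = 81%, 0.17 + 0.80 × 0.70 = 73%, or 0.17 + 0.80 × 0.50 = 57%. The respondents' result is the same in all three.

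**Step 8. The engagement inference.** On the planned figures, up to 80% of subscribers could ignore every message while respondents' answers stayed uniformly favourable. Both companion checks also use survey answers, so they are limited to the same group.

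**The case against.** The strongest reply is that subscribers is shorthand. The Introduction reports earlier survey results as percentages of subscribers, and one of the sources it cites is also the source of the 21.7% response rate. Expressing satisfaction also presupposes an answer. Read that way, hypothesis 4 is testable and very precise. This stands as far as it goes: the claim is testable among respondents, and a reader who concludes that it cannot be tested at all goes too far. But the article nowhere defines the denominator as respondents.

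Second, the engagement argument is raised about hypothesis 3, and symptom change is itself measured only in people who complete surveys. For them, favourable satisfaction answers do bear on whether they read the messages. This also stands, and it is why the inference should be limited rather than deleted. It does not carry over to subscribers as a whole, which is how the Discussion words it. Nor is satisfaction the only engagement evidence offered.

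Third, nonresponse is disclosed. A reader might infer that the authors overlooked it or confined it to wellness, pandemic impact and literacy. The text does not support that: the disclosure is general and those items are examples. What is missing is the link to satisfaction.

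Fourth, a reader might assume that only people still subscribed are surveyed, through a link in the messages. The article describes only a baseline invitation accompanying the first message. It does not say how or when satisfaction is asked, or whether people who opted out are included. The point does not need that assumption.

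Finally, the bounds in the working would arise in any survey with 20% response. They show what the data cannot establish. They are not evidence that satisfaction among subscribers is below 80%.

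**Conclusion.** The concern holds as a mismatch between the population named and the population measured. At the planned 20% response, 80% satisfaction among respondents is compatible with 16% to 96% of all subscribers, and no respondent result can confirm or refute the 80% claim for subscribers without an assumption about the other 240,000. For respondents the claim can be tested with negligible sampling error. The engagement inference is valid at most for respondents.

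This rests on the article's own planning figures, on voluntary participation, and on applying the general survey response rate to the satisfaction questions. If response to those questions is lower, the bounds widen. The argument about people who ignore messages also assumes that they rarely answer the survey, which is plausible but not documented. The documents do not support saying that satisfaction is overestimated by any particular amount. This is a matter of wording and interpretation for a secondary outcome, but it changes what the study may conclude.

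**What to change.** 1. Restate hypothesis 4, and the acceptability result in the Results section, as a proportion of survey respondents at each time point.
2. Beside that proportion, report the survey response rate and the number of opt-outs by STOP, both with all subscribers as the denominator, and the worst-case bounds r·s to r·s + (1 − r) for nonrespondents.
3. In the Discussion, extend the explicit nonresponse caution from prevalence to satisfaction.
4. In the same section, limit the engagement inference to respondents.

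Two shortcuts should be avoided. Absence of a STOP request is not proof of engagement, because a subscriber who silently ignores every message never sends one. Nor should every STOP be scored as dissatisfaction, except in an analysis labelled as a worst case, because the article records no reasons for leaving.

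The cost is a change of wording and a count of opt-out requests, which the service has to process anyway; whether the software exports them is not stated. No further data are needed from participants. The downside is a narrower and less favourable headline satisfaction claim.
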